## Abstract

**Background:**

Chronic fatigue syndrome (CFS) and major depressive disorder (MDD) are both debilitating but heterogeneous conditions sharing core features of fatigue, unrefreshing sleep, and impaired functioning. The aetiology of these conditions is not fully understood, and ‘best-practice’ treatments are only moderately effective in relieving symptoms. Unrecognised individual differences in the response to such treatments are likely to underlie poor treatment outcomes.

**Methods/design:**

We are undertaking a two-group, parallel, randomised controlled trial (RCT) comparing the effects of a personalised relaxation intervention on sleep quality, daytime symptoms, and functioning in patients with CFS (*n* = 64) and MDD (*n* = 64). Following identification of the method that best enhances autonomic responding (such as heart rate variability), participants randomised to the active intervention will practise their recommended method nightly for 4 weeks. All participants will keep a sleep diary and monitor symptoms during the trial period, and they will complete two face-to-face assessments, one at baseline and one at 4 weeks, and a further online assessment to evaluate lasting effects of the intervention at 2 months. Assessments include self-report measures of sleep, wellbeing, and function and monitoring of autonomic responses at rest, in response to the relaxation method and during nocturnal sleep. Treatment outcomes will be analysed using linear mixed modelling.

**Discussion:**

This is the first RCT examining the effects of a personalised relaxation intervention, pre-tested to maximise the autonomic relaxation response, in patients with unrefreshing sleep and fatigue attributed to CFS or MDD. Detailed monitoring of sleep quality and symptoms will enable sensitive detection of improvements in the core symptoms of these debilitating conditions. In addition, repeated monitoring of autonomic functioning can elucidate mechanisms underlying potential benefits. The findings have translational potential, informing novel, personalised symptom management techniques for these conditions, with the potential for better clinical outcomes.

**Trial registration:**

Australian and New Zealand Clinical Trials Registry (ANZCTR), ACTRN12616001671459. Registered on 5 December 2016.

**Electronic supplementary material:**

The online version of this article (10.1186/s13063-018-2763-8) contains supplementary material, which is available to authorized users.

## Background

Chronic fatigue syndrome (CFS) is a debilitating disorder characterised by prolonged medically unexplained, disabling fatigue, with concomitant unrefreshing sleep, as well as other constitutional and neurocognitive symptoms [1]. Some of these core symptoms are shared by patients with major depressive disorder (MDD), notably fatigue, unrefreshing sleep, and neurocognitive difficulties [2, 3]. Both CFS and MDD are prevalent conditions [4, 5], yet despite international research efforts, their pathophysiological basis remains obscure, in part reflecting heterogeneity within the syndromal diagnoses [6, 7]. The disease burden and costs associated with these disorders are substantial both for the individual and society [8, 9], yet available management strategies for both conditions have only partial efficacy [10–12].

Autonomic nervous system (ANS) dysfunction is a common feature of a wide range of medical and neuropsychiatric conditions including CFS and MDD [13–15]. The ANS comprises sympathetic and parasympathetic divisions. Broadly, the sympathetic division is concerned with energy-demanding processes during times of activity and stress (e.g. the ‘fight-or-flight response’), whereas the parasympathetic division (notably via action of the vagus nerve) is associated with vegetative and restorative functions. These two divisions operate together to maintain homeostasis. The heart is dually innervated by both the excitatory sympathetic and inhibitory parasympathetic (vagal) divisions, resulting in constant flux of the interval between heartbeats. This variation in inter-beat interval is referred to as heart rate variability (HRV) and is widely regarded as a sensitive and reliable non-invasive method of assessing autonomic function [16–18]. Optimal autonomic function is characterised by flexible adaptation to environmental challenges and a marked increase in vagal activity during rest (reflected by high HRV), whereas low HRV and a shift towards sympathetic dominance reflect a vigilant, defensive physiological state lacking dynamic flexibility, suggestive of a system under stress [19].

There is a growing body of literature linking constitutionally reduced HRV with sleep difficulties in neuropsychiatric conditions including CFS and MDD [13, 20, 21]. Specifically, low HRV (which persists even during sleep) correlates strongly with the core symptoms of unrefreshing sleep, fatigue, and cognitive impairment in CFS [14, 15]. Similarly, somatic symptoms of depression such as fatigue and sleeping difficulties are more closely associated with lowered HRV than other symptoms of depression [22, 23]. In light of the evidence supporting a role for reduced HRV in the manifestation of debilitating symptoms, therapeutic interventions targeting autonomic imbalance may be beneficial to patients affected by these and potentially other fatigue-related conditions.

In the absence of curative treatments for CFS and MDD, interventions are aimed at symptom management and functional improvements [24–28]. These interventions include variants of physical activity programs such as graded exercise therapy (GET) and cognitive-behavioural therapy (CBT) [10, 29–31]. In addition to these therapies, behavioural interventions including relaxation and mindfulness-based approaches [32–34] are increasingly utilised, and more recently HRV biofeedback [35, 36] has been explored in CFS and MDD. The beneficial effects of such techniques, including improvements in autonomic functioning, are thought to be mediated via their impact on neural circuits involved in self-regulation and adaptation [19, 37, 38].

Despite their widespread use, these psycho-behavioural interventions typically show only small to moderate effect sizes, with average response rates rarely exceeding 30% [10, 12, 25, 31, 33, 39]. Drill-down analyses have revealed subgroups of patients who do not respond or who respond unfavourably to such interventions [40, 41]. Although it is recognised that individuals can differ considerably in their response to both pharmaceutical and psycho-behavioural therapies [11, 40, 42], individual variation in response to common therapies in fatiguing illnesses has not been examined in any depth.

We recently reported the first detailed study of individual differences in ANS responses to a variety of relaxation methods in healthy individuals [43]. We found that engagement with four different methods (soothing white noise, classical music, paced breathing, and guided relaxation) elicited significant differences in vagal activity (HRV, continuously monitored). Close inspection of the results revealed diversity in individual response patterns across the four relaxation methods. Indeed, the method that elicited the greatest HRV response overall varied significantly between participants. Moreover, there was no close association between participants’ subjective evaluation of the relaxation methods and the method that elicited their optimal HRV response. Thus, to maximise health outcomes, it could be beneficial to pre-test participants in order to determine their optimal method, rather than relying solely on subjective responses or, as is common practice, employing a ‘one-size-fits-all’ approach.

### Study objectives

Extending our novel findings, we are now conducting a randomised controlled trial (RCT) comparing the effects of a personalised intervention (determined from each participant’s best autonomic response to three different relaxation methods: guided relaxation, gentle noise, and instrumental music) to a sleep- and symptom-monitoring control condition in patients experiencing chronic fatigue due to CFS or MDD. This study aims to facilitate new approaches in clinical practice and more meaningful health outcomes for patients suffering from chronic fatigue states. The inclusion of two different patient groups with debilitating fatigue will provide additional insights into the generalisability of benefits derived from such an intervention to other groups with fatiguing illnesses. The specific aims of this clinical trial are to:Determine the efficacy and specific benefits of a 4-week personalised relaxation intervention in terms of (a) subjective health outcomes and (b) restoration of autonomic balance in patients with CFS, and with MDD, compared to a sleep- and symptom-monitoring control conditionPerform a follow-up assessment 4 weeks after the completion of the intervention to document enduring health-related benefits that flow from participation in a personalised relaxation intervention (active group only).

It is hypothesised that the personalised relaxation intervention, pre-tested to maximise the participant’s autonomic relaxation response, will be substantively more effective in improving sleep quality as well as daytime fatigue, symptoms, and functioning than sleep and symptom monitoring only (no relaxation intervention). Additionally, it is expected that nightly practice of the intervention will improve autonomic functioning in patients suffering from both depression and fatigue. The findings from this research will facilitate a better understanding of the pathophysiological mechanisms operating in chronic fatigue states.

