### Data collection

All consenting participants complete two face-to-face assessments, 4 weeks apart, and a further set of questionnaires completed online 8 weeks after the initial assessment (Fig 2). At the first assessment (lasting approximately 90 min), participants’ demographic, health, and symptom information are documented. Autonomic activity at rest and in response to each of the relaxation methods (see below) is recorded. Results from this initial testing determine which method participants randomised to the intervention group will practise daily during the 4-week intervention (i.e. the method which induced the greatest increase in HRV for that participant). Before leaving, all participants are fitted with a non-invasive ambulatory bioharness (Equivital EQ-02, Hidalgo Ltd., Cambridgeshire, UK) for 24-h monitoring and issued a sleep/activity/symptom log to complete over the next 4 weeks (see subsequent paragraphs). The second assessment lasts approximately 45 min and consists of a briefer version of the initial assessments (i.e. assessment of health, symptoms, and autonomic activity). Those in the control arm will be offered the personalised intervention at this assessment. The third assessment consists of online self-report measures, including questionnaires about the participant’s sleep, symptoms, and current frequency of relaxation practice. This will allow us to assess possible enduring benefits of the intervention in the active group, and to determine whether subjective improvements are evident in the monitoring group who will have practised their assigned intervention for 4 weeks. Participants will be emailed a personalised link to the online questionnaire. An automated reminder email will be sent after 1 week and again after 2 weeks, if the participant has not completed the questionnaire. The online nature of this assessment will reduce inconvenience for the participants and hence minimise attrition.

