After the presentation of each relaxation method, participants are asked how relaxing they found the method (on a scale ranging from ‘not at all’ to ‘very’ relaxing) and whether they would expect the intervention to be helpful in reducing their symptoms (‘no’, ‘maybe’, ‘yes’). At the second assessment, participants in the intervention group are asked if they were satisfied with the intervention in improving their symptoms (on a scale ranging from ‘not at all’ to ‘completely’). At the 8-week online assessment, participants are asked if they have continued to practise their assigned relaxation method, and if so, how frequently.

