#### Sleep and symptom monitoring

Participants in the control condition complete the same assessments as the intervention group at baseline and at the 4 week follow-up. Control participants are informed that 4 weeks of symptom monitoring will precede allocation of a personalised relaxation method. During this period they are asked not to practise mindfulness or meditation activities. At the completion of the second assessment, participants in the control group will be offered their personalised intervention.

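### Aim 2 and the abstract attribute week-8 benefit to the intervention from the active group alone, but the design has no untreated comparator after week 4 and cannot give a controlled lasting effect

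*Protocol article*

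**What the plan says.** All places are in the protocol article.

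- **Study objectives, second aim.** A follow-up four weeks after the end of the intervention is meant "to document enduring health-related benefits that flow from participation in a personalised relaxation intervention (active group only").
- **Abstract, Methods/design.** The same assessment is "a further online assessment to evaluate lasting effects of the intervention at 2 months".
- **Data collection**, on the second (week-4) assessment: "Those in the control arm will be offered the personalised intervention at this assessment". **Sleep and symptom monitoring** repeats this: "At the completion of the second assessment, participants in the control group will be offered their personalised intervention".
- **Data collection**, on the third (week-8) assessment. It has two purposes: to look for possible enduring benefit in the active group, and to see "whether subjective improvements are evident in the monitoring group who will have practised their assigned intervention for 4 weeks".
- **Self-report measures.** At week 8 "participants are asked if they have continued to practise their assigned relaxation method", and how often.
- **Personalised relaxation intervention.** Recordings can be downloaded to the participant's own device. No end to access is described.
- **Outcomes.** The primary outcomes are assessed at week 4.
- **Randomisation, allocation, and blinding.** Neither participants nor the assessing researcher are blinded.

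**The concern.** Saying that benefits flow from participation, or that an assessment evaluates lasting effects of an intervention, is a causal statement. It needs a comparison with what would have happened without the intervention. Up to week 4 the monitoring arm supplies that comparison. After week 4 it does not, because that arm is offered the same intervention.

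What remains for the second aim is a before-after change in unblinded participants on self-report questionnaires. Published from a randomised trial as enduring benefit, it would be read as randomised evidence. The stakes are practical: Ethics and dissemination says that if results point towards benefit, links to the recordings will go to the two recruiting institutions and other stakeholders.

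The Data collection question about the monitoring arm has the same weakness. It is also a before-after reading, and it treats an offer as if it had been taken up for four weeks.

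**Working it through.** **1. What is compared with what**

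| | Weeks 0 to 4 | Weeks 4 to 8 |
|---|---|---|
| Active arm | assigned nightly practice | practice optional, use only recorded |
| Control arm | monitoring only | offered the intervention, uptake not known in advance |
| Untreated comparator | yes, randomised | none |

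The active arm's change to week 8 is therefore the sum of treatment effect, natural course, regression to the mean, expectancy and the effect of any continued practice. One observed mean cannot separate these components. Because practice may continue, week 8 is not reliably a time after the intervention has ended, so carry-over and ongoing use are also confounded. The recorded frequency of practice does not solve this: it is chosen after randomisation, so adjusting for it or splitting by it does not restore a randomised comparison.

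**2. How easily a within-arm change appears with no treatment effect (illustration)**

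The plan gives no figure to reproduce here.

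- From Sample size estimates: 64 per arm and attrition up to 10%, so 64 × 0.9 = 57.6, taken as 57 completers.
- Assumed, not in the documents: true treatment effect zero; drift towards improvement m of 0.1 to 0.5 SD; baseline to week-8 correlation r of 0.5 or 0.7; a two-sided test at 0.05.

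Formula: the SD of change is √(2(1 − r)), in baseline SD units. The probability of a significant improvement is Φ(m√57 / √(2(1 − r)) − 1.96).

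Example with m = 0.3, r = 0.5: SD of change = 1; 0.3 × 7.55 = 2.265; Φ(2.265 − 1.96) = Φ(0.305) = 0.62.

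| Drift m | r = 0.5 | r = 0.7 |
|---|---|---|
| 0.1 SD | 0.11 | 0.16 |
| 0.2 SD | 0.33 | 0.50 |
| 0.3 SD | 0.62 | 0.83 |
| 0.5 SD | 0.97 | 0.998 |

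At 0.013, the level used in Sample size estimates, the same grid runs from 0.04 to 0.99. If patients drifted towards worse instead, the within-arm change would understate the effect.

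**3. Whether a between-arm contrast at week 8 would help**

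It can be computed, but it compares immediate with delayed offer, not intervention with none. Assume the active arm keeps all of a 1 SD effect (the size named in Sample size estimates) and controls gain a fraction c of it after week 4. The contrast is then 1 − c. Power at two-sided 0.013 with 57 per arm is Φ((1 − c)√(57/2) − 2.484).

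| c | Contrast | Power |
|---|---|---|
| 0.25 | 0.75 SD | 0.94 |
| 0.50 | 0.50 SD | 0.57 |
| 0.75 | 0.25 SD | 0.13 |
| 1.00 | 0 | 0.013 |

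A fully retained effect could thus show as no difference between arms.

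**The case against.** The strongest reply is that the limit is largely in the open. The second aim speaks of documenting, whereas the first aim speaks of determining efficacy. It names the active group as its only source, Data collection calls the enduring benefits possible, and continued practice is recorded. Offering controls the intervention after the primary endpoint is a stated design choice. Nowhere does the article say that a within-group change will be reported as a randomised effect, and no week-8 significance test is described. All of this is true. It makes the point one of wording and claim rather than of design. It does not remove the causal attribution in the aim and the abstract, which the design cannot support.

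Three stronger readings are tempting and are not supported.

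- *Nothing about durability can be learned.* Maintenance within the active arm from week 4 to week 8 can be described, and an immediate-versus-delayed contrast can be estimated. Only the controlled effect against no intervention is out of reach.
- *Week-8 data will dilute the trial's main arm effect in the mixed model.* Outcomes places the primary outcomes at week 4, and the second aim uses one arm only, so no such pooling is described.
- *The second aim contradicts Data collection, because everyone completes week 8.* Collecting data from all participants while limiting one question to one arm is consistent.

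The illustration is also fairly open to challenge. The eligibility criteria set no severity score, so the documents give no basis for a particular amount of drift. That is why a range is shown and no single value is put forward.

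**Conclusion.** The point holds in limited form. As worded, the second aim and the abstract draw a causal conclusion about week 8 from an uncontrolled before-after change. This follows from the text alone: the week-4 offer to controls, optional continued practice in the active arm, and no other comparator.

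The size cannot be fixed from the documents. Under the assumptions shown, the chance of a significant within-arm improvement with no treatment effect ranges from about 0.11 to above 0.99. The conclusion does not depend on where in that range the truth lies.

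The randomised week-4 comparison, which carries the primary outcomes, is untouched. The matter should be corrected, but it limits a secondary aim and does not threaten the trial's main result.

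**What to change.** - Reword the second aim, the abstract sentence and the two week-8 statements in Data collection as descriptive.
- Report week-8 status and the week 4 to 8 change by arm, with confidence intervals. Label the active arm's result as maintenance under optional continued practice. Label the control arm's result as uncontrolled change after an offer of the intervention, with all controls included whatever their uptake.
- Make no efficacy or enduring-benefit claim from week 8, and confine efficacy conclusions to the week-4 randomised contrast.
- If controls' week 4 to 8 change is set against their own week 0 to 4 change, label it exploratory and uncontrolled. It is itself a before-after comparison, and regression to the mean would fall mainly in the first interval.

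No new data and no change to what participants are offered are needed. The cost is a weaker secondary claim.

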## Methods/design

### Study design

This study is a two-parallel group RCT comparing a personalised relaxation intervention to a sleep- and symptom-monitoring control condition. All assessments are conducted at the University of New South Wales Sydney (UNSW), Australia. The trial has been registered on the Australian and New Zealand Clinical Trials Registry (ANZCTR, ACTRN12616001671459). All dimensions of the study protocol have been described adhering to the Standard Protocol Items: Recommendations for Interventional Trials (SPIRIT) checklist (Additional file 1; Fig. 1).

**Fig. 1 Fig1:**
[figure not shown]
Schedule of enrolment, interventions, and assessments (Standard Protocol Items: Recommendations for Interventional Trials (SPIRIT) diagram)

### Sampling and recruitment

Potential participants are screened by email or telephone to ensure they meet eligibility criteria before proceeding to enrolment. Individuals are eligible to participate if they are aged between 18 and 65 years at the time of assessment; have been diagnosed by a physician or psychiatrist to meet international diagnostic criteria for CFS [1] or MDD with fatigue as a significant feature as defined by Diagnostic and Statistical Manual of Mental Disorders, 5^th^ edition (DSM-V) diagnostic criteria [44]; have self-reported normal hearing; sufficient English language proficiency to complete questionnaires and understand instructions; and a willingness to participate and comply with the longitudinal nature of the study. Individuals who are concurrently engaged in relaxation or mindfulness-based therapies; are pregnant; have other significant illnesses or major diagnoses such as primary sleep disorder, heart conditions, uncontrolled diabetes, chronic infections, or psychotic disorders; or who take regular medications that affect autonomic activity, including beta blockers and anti-hypertensives, are excluded from the study. Use of anti-depressant medication or hormonal contraception is recorded, but is not exclusionary.

Patients with CFS are recruited from an academic tertiary referral clinic which specialises in the management of chronic fatigue states (UNSW Fatigue Clinic in Sydney, Australia) via advertisements placed in clinic waiting rooms and targeted email advertisement distribution to the clinic’s opt-in volunteer research register. Participants with MDD are recruited from the Black Dog Institute (BDI), a mental health research centre and clinic in Sydney, via online advertisements and email distribution to the BDI volunteer research register.

